**Methods/Design:**

We propose a cluster-randomised, controlled trial to evaluate trauma care enhanced with a formalised TTS procedure. Currently, 20 to 25% of trauma patients routinely have a TTS performed. We expect this to increase to at least 75%. The design is for 6,380 multi-trauma patients in approximately 16 hospitals recruited over 24 months. In the first 12 months, patients will be randomised (by hospital) and allocated 1:1 to receive either the intervention (Group 1) or usual care (Group 2). The recruitment for the second 12 months will entail Group 1 hospitals continuing the TTS, and the Group 2 hospitals beginning it to enable estimates of the persistence of the intervention. The intervention is complex: implementation of formal TTS form, small group education, and executive directive to mandate both. Outcome data will be prospectively collected from (electronic) medical records and patient (telephone follow-up) questionnaires. Missed injuries will be adjudicated by a blinded expert panel. The primary outcome is missed injuries after hospital discharge; secondary outcomes are maintenance of the intervention effect, in-hospital missed injuries, tertiary survey performance rate, hospital and ICU bed days, interventions required for missed injuries, advanced diagnostic imaging requirements, readmissions to hospital, days of work and quality of life (EQ-5D-5 L) and mortality.

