### Randomisation

Participating hospitals (clusters) will be 1:1 randomised to either immediate (Group 1) or delayed (Group 2) introduction of TTS (Figure 1), using computer-generated random number function. Group 1 will implement formalised TTS in the first 12 months, with continuation of formalised TTS in the second 12 months. Group 2 hospitals will continue routine trauma care in the first 12 months followed by implementation of formalised TTS in the second 12 months. A statistician not involved with the data collection will be involved to conduct the randomisation. Results of the randomisation will be communicated to the operations manager of the study, who will inform the participating hospitals of the allocation. All patients of individual hospitals will receive the same treatment arm.

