### Outcome measures

The primary outcome is Type III missed (Post-hospital discharge) injury rate. This study aims to compare the effect of a formalised TTS compared to routine care on missed injury rates after hospital discharge (type III).

Secondary outcomes are:Maintenance of intervention effect (comparing two 12-month periods in Group 1)*During Hospital Stay*In-hospital missed injury rate (Type I and II combined)Proportion of TTS performedHospital bed days, ICU bed days*During Follow-up (1,6 and 12 months post hospital discharge)*Clinically significant missed injuries (as determined by expert panel)Interventions required for delayed diagnosis (Type I and II) or missed injuries (Type III)Diagnostic imaging usage (CT, MRI, USS)Predefined complications of care and injury (see above)Readmissions to hospitalDays off workQuality of life (EQ-5D-5 L)Days off workMortality

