### Statistical analysis and sample size

The primary analysis will be by intention-to-treat (ITT). Per-protocol analyses will also be performed, based on all patients completing 1, 6 and 12 months follow-up. Based on our prospective study [16], comparing routine care with the formalised TTS group, we anticipate a decrease in post discharge (Type III) injuries from 14% to 9%. We foresee this will be accompanied by an increase of in-hospital injury detection (missed injury Type I and II combined) from 4% to 9%.

The sample size for a cluster-randomized trial requires adjustment of the number of patients that a corresponding individually randomized trial would have needed. This is due to variation between the clusters, and results in a correction using the intra-cluster correlation coefficient (ICC) [21]. Using an alpha of 0.05 and a power of 0.80, a sample size of 638 patients per group, with 1-year follow-up completed, would be required if individually randomised. Our previous study [17] achieved a telephone follow-up rate of 40% at 6 months. Extrapolating a similar conservative follow-up rate at 12 months, a total of 3,190 patients will be required (1,595 for each cohort) to answer the primary hypothesis. To separately answer a before-and-after comparison in Group 2 hospitals a similar sample is required. This results in a sample of 6,380 patients, with complete 1-year follow-up in at least 2,552. Since approximately 0.4% [22] of all ED presentations consist of multi-trauma patients, approximately 1,600,000 ED presentations will be required. For an approximate 24-month recruitment period, this equates to 16 hospitals that have an average annual census of 50,000 presentations. Based on this sample size, the maximum ICC that can be present before the power of the study is reduced below 80% is dependent on cluster size and numbers and presented in Table 3*.*

**Table 3 Tab3:** **Approximate maximum intra-class correlation (ICC) for various cluster sizes and number of intervention hospitals to answer primary hypothesis**

**Number of intervention (and control) hospitals**	**Average size of cluster**	**Maximum ICC to have 80% power to detect 5% difference**
8	400	0.01
15	400	0.02
21	400	0.03
9	300	0.01
15	300	0.02
22	300	0.03
10	200	0.01
16	200	0.02
23	200	0.03

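### Maintenance is defined by a Year 1 to Year 2 change within Group 1 that calendar time confounds; the concurrent randomised Year 2 contrast is not specified, and the Group 2 before-and-after result should be labelled uncontrolled

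*Protocol article*

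**What the plan says.** All references are to the Protocol article.

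- **Schedule (Randomisation).** Hospitals "will be 1:1 randomised to either immediate (Group 1) or delayed (Group 2) introduction of TTS". For the immediate arm, "Group 1 will implement formalised TTS in the first 12 months, with continuation of formalised TTS in the second 12 months". For the delayed arm, "Group 2 hospitals will continue routine trauma care in the first 12 months followed by implementation of formalised TTS in the second 12 months".
- **Maintenance (Outcome measures).** The outcome is "Maintenance of intervention effect (comparing two 12-month periods in Group 1"). The Aims and hypotheses section hypothesises that the effect will be maintained.
- **Group 2 (Statistical analysis and sample size).** The sample is doubled from 3,190 to 6,380 for this reason: "To separately answer a before-and-after comparison in Group 2 hospitals a similar sample is required".
- **Tests (same section).** Chi-square tests for proportions and independent t-tests for continuous variables are named, with no term for period. The section calls both within-group comparisons pre- and post-comparisons. It states adequate power for the Group 2 one but not for the Group 1 one.
- **Purpose of Year 2 (Abstract, Methods/Design).** The second year has "Group 1 hospitals continuing the TTS, and the Group 2 hospitals beginning it to enable estimates of the persistence of the intervention".

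**The concern.** A comparison of Year 2 with Year 1 inside one randomised group cannot separate the intervention from anything else that changes between the years, such as imaging practice, case mix or staffing. In Group 1, a general fall in missed injuries would hide a fading effect and a general rise would look like fading. In Group 2, a general fall would be credited to the TTS. The Background treats the existing non-randomised evidence, including the team's own before-and-after study, as inconclusive.

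The Abstract presents the two-group Year 2 layout as the means of estimating persistence, yet the outcome definition uses Group 1 alone. What is at stake is the maintenance conclusion and the weight given to the Group 2 result, for which half of the sample is justified. Both are secondary questions.

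**Working it through.** **1. The plan's own figures reproduce.** Inputs from Statistical analysis and sample size: 14% against 9%, alpha 0.05, power 0.80, 40% follow-up. I take alpha as two-sided, which the text does not state.

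n = [1.960·√(2·0.115·0.885) + 0.842·√(0.14·0.86 + 0.09·0.91)]² / 0.05² = 638 per group.

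638/0.40 = 1,595; ×2 = 3,190; ×4 = 6,380; 0.40 × 6,380 = 2,552. All agree with the article. The arithmetic is not in question.

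**2. What each contrast estimates.** Let b be the routine-care rate in Year 1, y the calendar drift common to all hospitals, T1 the effect of TTS in its first year of use and T2 its effect in the second. Assume for now that T1 is the same in both groups.

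| | Year 1 | Year 2 |
|---|---|---|
| Group 1 | b + T1 | b + y + T2 |
| Group 2 | b | b + y + T1 |

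- Primary, Group 1 − Group 2 in Year 1: T1. No drift.
- Planned maintenance, Group 1 Year 2 − Year 1: (T2 − T1) + y. Drift enters in full.
- Planned Group 2 before-and-after: T1 + y. Drift enters in full.
- Unspecified, Group 1 − Group 2 in Year 2: T2 − T1. Common drift cancels.

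Four cells and four unknowns make the model saturated. A joint model with a year term therefore returns the two between-group differences and adds no control to the Group 2 change.

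**3. Effect of drift on the planned tests.** The documents give no drift, so 1, 2 and 3 points are assumptions. The test is a two-sided chi-square with 638 against 638 completers, patients treated as independent, no true effect, and a falling rate:

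| Assumed drift | Group 1, from 9% | Group 2, from 14% |
|---|---|---|
| 1 point | 10% | 8% |
| 2 points | 26% | 19% |
| 3 points | 53% | 37% |

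The entries are the chance of a significant result; the nominal rate is 5%. A drift of 1 to 2 points is 20% to 40% of the 5-point target.

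**4. Precision.** Inputs: 16 hospitals (8 per group) and ICC 0.01, both from the article; p = 9% in both cells; four equal cells of 638 completers, so m = 638/8 = 79.75 per hospital and year. The between-period correlation r is assumed.

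- Year 2 between groups: design effect = 1 + 78.75 × 0.01 = 1.79. SE = √(2·0.0819/638 × 1.79) = 2.14 points. The 95% half-width is 1.96 × 2.14 = 4.2 points, and the difference detectable with 80% power is 2.80 × 2.14 = 6.0 points (5.3 at ICC 0.005, 7.2 at ICC 0.02).
- Within Group 1: SE = √{(2/8)·[0.0819·0.99/79.75 + 0.0819·0.01·(1 − r)]}. This gives 1.59 at r = 1.0, 1.72 at r = 0.8 and 1.89 at r = 0.5. Detectable differences are 4.5, 4.8 and 5.3 points.
- Complete loss of effect (9% back to 14%), Year 2 contrast: SE = √[(0.0819 + 0.1204)/638 × 1.79] = 2.38 points. 5/2.38 − 1.96 = 0.14, so power is about 55%.

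**5. Bias against precision.** At r = 0.8, root mean squared error within Group 1 is √(1.72² + 1²) = 1.99 for 1 point of drift and √(1.72² + 2²) = 2.64 for 2 points, against 2.14 for the Year 2 contrast. Break-even drift is √(2.14² − 1.72²) = 1.27 points.

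**The case against.** The strongest reply is that the replacement is weak. Its detectable difference exceeds the whole anticipated effect, and below about 1.3 points of drift the planned contrast has the smaller total error. This stands, and it is why the Year 2 contrast should be reported as an estimate with its interval beside the within-group change. It does not make the planned contrast interpretable alone, because the drift is unknown and the trial cannot estimate it without further assumptions.

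A second reply is that the estimands differ. The plan asks whether Group 1 hospitals hold their own result, whereas the Year 2 contrast compares different hospitals. A difference near zero could also arise if the TTS does nothing. Poor first-year uptake in Group 2, which starts after a year of trial data collection, could likewise distort the comparison. This stands too. The contrast must be read with the primary result and with TTS performance in both groups, and it assumes that first-year TTS is similar in both.

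A third reply is that the scripted interview, the standardised form and the central blinded panel limit drift in measurement. They do, but they do not control change in case mix or care. The article also already concedes low power for maintenance; that is a statement about precision and does not disclose the bias.

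Two stronger readings are tempting. A reader might infer that the design holds a randomised contrast for the Group 2 effect as well. It does not: every hospital uses TTS in Year 2, so no concurrent routine-care comparator exists. A reader might also infer that the second half of the sample is wasted. That does not follow, since Year 2 patients are what make the concurrent persistence contrast possible.

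**Conclusion.** The point holds for the secondary questions. The maintenance outcome and the Group 2 before-and-after comparison are each fully confounded with calendar time as defined, and the stated tests do not address it. For maintenance, a randomised concurrent contrast exists and is not specified, although the Abstract's wording points towards it. For Group 2 there is no such remedy, so the result can only be labelled for what it is.

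The bias equals whatever drift occurs: 1 to 2 points on a 5-point target if drift is 1 to 2 points, which is an assumption. Removing it raises the standard error from 1.6–1.9 to about 2.1 points, given ICC 0.01, about 638 completers per cell and a between-period correlation of 1.0 to 0.5. The cancellation covers only drift common to both groups. The Year 1 comparison of Group 1 with Group 2, which answers the primary hypothesis, is not affected. This is an inexpensive improvement, not a flaw in the trial's main question.

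**What to change.** 1. In Outcome measures, define the randomised estimate of persistence as the Group 1 minus Group 2 difference in the second 12 months (second-year against first-year TTS), with a 95% confidence interval that allows for clustering by hospital. State that it is for estimation and is not powered as a test.
2. Report the within-Group-1 change from Year 1 to Year 2 beside it, labelled as uncontrolled supporting evidence.
3. Label the Group 2 before-and-after result as uncontrolled, and do not present it as a separate confirmation of the TTS effect.
4. State the assumption that first-year TTS is similar in both groups, and show TTS performance by group and year so that readers can judge it. These data are already to be collected.

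The primary analysis and the sample size do not change. The cost is wording and one additional estimate from data already planned; recruitment had not begun when the article was written (Trial status). The price is a wider interval, with a half-width of about 4.2 points at ICC 0.01.

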### Statistical analysis and sample size

The primary analysis will be by intention-to-treat (ITT). Per-protocol analyses will also be performed, based on all patients completing 1, 6 and 12 months follow-up. Based on our prospective study [16], comparing routine care with the formalised TTS group, we anticipate a decrease in post discharge (Type III) injuries from 14% to 9%. We foresee this will be accompanied by an increase of in-hospital injury detection (missed injury Type I and II combined) from 4% to 9%.

The sample size for a cluster-randomized trial requires adjustment of the number of patients that a corresponding individually randomized trial would have needed. This is due to variation between the clusters, and results in a correction using the intra-cluster correlation coefficient (ICC) [21]. Using an alpha of 0.05 and a power of 0.80, a sample size of 638 patients per group, with 1-year follow-up completed, would be required if individually randomised. Our previous study [17] achieved a telephone follow-up rate of 40% at 6 months. Extrapolating a similar conservative follow-up rate at 12 months, a total of 3,190 patients will be required (1,595 for each cohort) to answer the primary hypothesis. To separately answer a before-and-after comparison in Group 2 hospitals a similar sample is required. This results in a sample of 6,380 patients, with complete 1-year follow-up in at least 2,552. Since approximately 0.4% [22] of all ED presentations consist of multi-trauma patients, approximately 1,600,000 ED presentations will be required. For an approximate 24-month recruitment period, this equates to 16 hospitals that have an average annual census of 50,000 presentations. Based on this sample size, the maximum ICC that can be present before the power of the study is reduced below 80% is dependent on cluster size and numbers and presented in Table 3*.*

**Table 3 Tab3:** **Approximate maximum intra-class correlation (ICC) for various cluster sizes and number of intervention hospitals to answer primary hypothesis**

**Number of intervention (and control) hospitals**	**Average size of cluster**	**Maximum ICC to have 80% power to detect 5% difference**
8	400	0.01
15	400	0.02
21	400	0.03
9	300	0.01
15	300	0.02
22	300	0.03
10	200	0.01
16	200	0.02
23	200	0.03

This calculation is consistent with a previous study specifically examining the ICC in trauma receiving hospitals. ICC varied depending on outcome, but the average ICC for blunt trauma the ICC was 0.01 [23]. Assuming an average cluster size of 250 patients, this would mean a total of 3,440 patients would require recruitment (approximately 14 clusters) for the primary hypothesis.

The study is adequately powered for the primary hypothesis, and for several secondary outcomes, such as pre- and post-comparison in Group 2, but not for the pre- and post- comparison in Group 1, measuring maintenance of the intervention effect.

De-identified data will be analysed using SPSS v20.0 software (SPPS Inc, Chicago, IL, USA). For continuous variables, we will use an independent *t*-test and chi-square test will be used to compare differences in proportions. All results will be presented with 95% confidence intervals.

Health economic analyses will include a within trial incremental cost-effectiveness evaluation of formal TTS versus standard care. The outcome measure, incremental cost-effectiveness ratio, directly compares the difference in costs between the formal TTS and standard care with the difference in health related quality of life. Health-related quality of life will be measured in quality adjusted life years (QALYs) derived from changes in EQ-5D-5 L measured at multiple time points. A cost-effective threshold of $AUD 50,000 per QALY will be used to determine whether the intervention was cost-effective and a cost-effectiveness acceptability analysis will be conducted using a range of threshold values from $20,000 to $100,000. A 95% confidence interval around the incremental cost-effectiveness ratio will be estimated using bias-adjusted bootstrapping. In addition, sensitivity analyses and sub-group analyses will be conducted to identify the parameters and patient characteristics that affect the likelihood of the intervention being cost-effective. A *P* value of 0.05 or less will be deemed statistically significant.

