A retrospective study [15] in our Australian level II trauma facility found poor compliance to routine TTS and identified a lack of data regarding post-discharge missed injuries. A subsequent, pragmatic, prospective before-and-after study [16] evaluated the implementation of a formalised TTS procedure by measuring missed injury rates during a hospital stay (Type I and II) as well as after discharge (Type III). The in-hospital missed injury rate (Type I and II combined) was similar for both groups (Pre: 3.8% versus Post: 4.8%), as were Type III missed injuries at 1 month (Pre: 13.7% versus Post: 11.5%), and 6 months (Pre: 3.8% versus Post: 3.3%). Although there was a substantial increase in tertiary survey performance (27% versus 42%, *P* < 0.001), this may not have been enough to detect any potential differences in missed injury rates if they exist.

Missed injuries may be minor or only require conservative treatment. Therefore, the focus ideally should be on clinically significant missed injuries. Few studies have defined ‘clinically significant’ *post hoc*, [7,11,12] with most studies not providing any definition. Whilst the incidence of clinically significant missed injuries is unknown, they are more likely to lead to prolonged morbidity or mortality. Although mortality as a result of missed injuries is conceivably rare, our prospective study indicated that approximately 1% of the cohort required a surgical intervention for injuries detected after the hospital discharge. [16].

Current international guidelines such as Early Management for Severe Trauma (EMST) do mention consideration of tertiary surveys, but do not mandate or formalise their implementation. [17] This may be the result of their focus on *early* trauma care, where the tertiary survey by can be conducted up to 24 hours after ED assessment.

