### Data collection

Data collection processes are the same for both Groups. The prospectively identified eligible patients will have their primary and secondary survey performed in the ED. All clinical reviews (including ward rounds) in the first 24 hours on the ward after surgical or interventional radiology intervention will be documented using a previously used [15,16] data collection tool (Additional file 2: Appendix B). Data will be collected by a trained research nurse will include demographic variables, mechanism of injury, Australasian Triage Scale category (ATS) [18] and Glasgow Coma Scale (GCS) on arrival in ED. The Injury Severity Score (ISS) [19] will be calculated after discharge. An ISS score of greater than 15 indicates severe trauma.

Data related to the inpatient admission will include whether a (formalised) TTS is documented during admission and which components of the TTS are performed. A list of injuries, newly detected injuries and changes in management will be collected. A central blinded panel of experts, comprised of at least two emergency physicians and 2 (trauma) surgeons, will class newly detected injuries in-hospital as Type I, Type II or not a new injury (see Table 2). A scripted follow-up telephone interview (Additional file 3: Appendix C) will be conducted at 1, 6 and 12 months after discharge. This follow-up interview will collect data on (Type III) missed injuries after discharge, complications of the injury (parasthaesia, chronic pain) or complications of care (postoperative infections and venous thrombo-embolism), return to pre-injury function, and a validated quality of life (QoL) questionnaire (EuroQoL EQ-5D-5 L [20]).

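### The primary outcome has no time window, and the sample size pairs a 1-month event rate with 12-month completers and a 6-month follow-up rate

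*Protocol article*

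**What the plan says.** Under Outcome measures the article states: "The primary outcome is Type III missed (Post-hospital discharge) injury rate". It gives no assessment time and no window. The label naming 1, 6 and 12 months in that section heads a group of secondary outcomes. The Abstract and the Aims and hypotheses add no time either. Under Data collection, the telephone interview that asks about Type III injury "will be conducted at 1, 6 and 12 months after discharge".

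Under Statistical analysis and sample size, the planning rates are introduced with "Based on our prospective study [16], comparing routine care with the formalised TTS group", followed by "we anticipate a decrease in post discharge (Type III) injuries from 14% to 9" (per cent). The same section requires 638 patients per group who have completed one year of follow-up. It cites a 40% telephone follow-up rate at 6 months and then proceeds by "Extrapolating a similar conservative follow-up rate at 12 months" to 1,595 per cohort, 3,190 for the primary hypothesis and 6,380 overall. It concludes that power is adequate for the primary hypothesis.

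The Background reports the prior study's results: "Type III missed injuries at 1 month (Pre: 13.7% versus Post: 11.5%), and 6 months (Pre: 3.8% versus Post: 3.3" (per cent). No 12-month rate is given anywhere.

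**The concern.** Three inputs to one calculation come from three different times. The event rate is a 1-month figure, the patients counted are 12-month completers, and the retention rate was measured at 6 months. The article discloses that the retention rate is carried from 6 to 12 months. It does not disclose that this is then combined with a 1-month event rate.

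The prior rates cannot be cumulative in one fixed set of patients, because a cumulative proportion cannot fall from 13.7% to 3.8%. They are best read as rates per interview, so the planning rate depends heavily on the window chosen.

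Two things are at stake. The statement that the trial is adequately powered cannot be checked until the endpoint is fixed. And an open window leaves more than one analysis that could be called primary once data are in hand. A primary endpoint's time frame is not a detail usually left to an analysis plan, and here the published sample size depends on it.

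**Working it through.** **Inputs.** Control and intervention rates 14% and 9%, evaluable number 638 per group, and follow-up 40% (Statistical analysis and sample size). Prior routine-care rates 13.7% at 1 month and 3.8% at 6 months (Background). The section states "Using an alpha of 0.05 and a power of 0.80"; it does not say whether the test is two-sided, but two-sided reproduces its figure.

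**Formula** (two proportions, pooled variance under the null, no continuity correction), with p̄ the mean of p1 and p2:

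n per group = [1.960·√(2p̄(1−p̄)) + 0.842·√(p1(1−p1)+p2(1−p2))]² / (p1−p2)²

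**Reproducing the plan.** p1 = 0.14, p2 = 0.09, p̄ = 0.115:

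- 1.960·√0.20355 = 0.884 and 0.842·√0.2023 = 0.379
- (0.884 + 0.379)² / 0.0025 = 638
- 638 / 0.40 = 1,595; × 2 = 3,190; × 2 again = 6,380; completers 4 × 638 = 2,552

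Every stated figure is matched exactly. The fault is not in the arithmetic.

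**Which endpoint do the inputs describe?**

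- 14%: matches 13.7% at 1 month, and no other Type III rate reported. This is an inference, since the sample size section does not label the rate.
- 638: patients with one year of follow-up.
- 40%: retention at 6 months, assumed unchanged at 12.

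**What 638 per group delivers under each candidate endpoint.** Power = Φ{[(p1−p2)·√638 − 1.960·√(2p̄(1−p̄))] / √(p1(1−p1)+p2(1−p2))}. Two-sided 0.05, before any clustering.

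| Endpoint | Rates | n per group for 80% | Power with 638 |
|---|---|---|---|
| Plan as stated | 14% vs 9% | 638 | 80% |
| 1 month, unrounded, 5-point drop | 13.7% vs 8.7% | 624 | 81% |
| Cumulative, 5-point drop | 17.5% vs 12.5% | 800 | 71% |
| Cumulative, proportional drop | 17.5% vs 11.25% | 494 | 89% |
| Later interview only, proportional drop | 3.8% vs 2.44% | 2,577 | 29% |

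The proportional drop uses the plan's own ratio: 17.5 × 9/14 = 11.25 and 3.8 × 9/14 = 2.44. The 17.5% is 13.7% + 3.8%. It assumes that no patient is counted at both interviews, that the two rates can be added although different numbers were reached, and that nothing new is reported at 12 months. If every 6-month case had already been reported at 1 month, the cumulative rate to 6 months would stay at 13.7%. A 5-point drop from 3.8% is impossible.

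**Retention.** Recruitment for the primary comparison is 2 × 638 / retention. If 1 month is primary and 1-month retention were 50%, 60% or 70% (assumed; no 1-month retention is given), it would be 2,552, 2,128 or 1,824 instead of 3,190. If 12-month completion is needed and retention were 30% (also assumed), it would be 4,254.

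**The case against.** The best defence is that the intended endpoint can be worked out. Table 1 defines Type III injury as one missed throughout the hospital stay, which is an event and not a state that lapses. The sample size is stated for patients with a year of follow-up. Together these suggest any Type III injury reported up to 12 months. On that reading the control rate is at least the 1-month rate, and 638 per group is roughly adequate or better before clustering if the reduction is proportional. The extrapolation of the 40% is also stated openly. It is an assumption, not a contradiction.

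Much of this stands, and it rules out several stronger conclusions that a reader might draw:

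- *That the trial has only about 29% power.* That needs an analysis restricted to injuries reported at a later interview, with a rate no higher than at 6 months. Nothing in the article proposes this, and no 12-month rate is given.
- *That early reports from patients lost later would be discarded.* The primary analysis is by intention to treat. Completing all three interviews defines only the per-protocol set.
- *That 12-month follow-up must be below 40%.* The documents give no figure for further loss. What can be said is that assuming no further loss over six more months is not evidently conservative.
- *That 1 month must be the primary time.* It is where the 14% comes from, but a cumulative 12-month outcome is equally coherent and may be closer to the intent.

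The defence does not remove the mismatch. The article never says that the outcome is cumulative, and if it is, 14% is a 1-month figure and not the planning rate for that outcome.

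**Conclusion.** The point holds. The primary outcome lacks a window, and the stated 638, 1,595 and 3,190 combine inputs from different endpoints. The claim of adequate power therefore attaches to no single defined outcome. The direction of the error is not fixed: a 1-month endpoint may be over-recruited for attrition, a cumulative endpoint has about 71% or 89% power depending on how the effect is expressed, and a later-interview rate alone would leave about 29%. Across these readings the required number per group runs from about 494 to about 2,577.

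The 14% to 1-month match is an inference from the article's own figures. The cumulative and later-interview results rest on the assumptions stated with the table. None of the figures allows for clustering, which would lower every power shown and is a separate matter. So is whether the anticipated size of the effect is realistic.

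**What to change.** In Outcome measures, state one primary window. Two choices are coherent:

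- definite or likely Type III missed injury reported by the 1-month interview; or
- definite or likely Type III missed injury reported at any interview up to 12 months, counting any report.

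Then take both the planning event rate and the retention rate from that window, restate the sample size and power on that basis, and make the other windows secondary. The 1-month choice keeps the 14% but needs a 1-month retention figure, and it moves late-recognised injuries to a secondary outcome. The cumulative choice keeps them in the primary outcome but needs a cumulative control rate to 12 months and a 12-month retention rate. Neither is in the article, so each should be given as an assumption with a range.

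The cost is one sentence and a restated power figure, which may be less favourable. Trial status says that recruitment has not begun, so the change can be made before any outcome data exist.

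### The requirement of 3,440 patients in about 14 clusters at ICC 0.01 does not follow from the protocol's own 638 per group and contradicts its Table 3

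*Protocol article*

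**What the plan says.** All the relevant text is in the protocol article under Statistical analysis and sample size, except the allocation, which is under Randomisation.

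- Individually randomised size: "Using an alpha of 0.05 and a power of 0.80, a sample size of 638 patients per group, with 1-year follow-up completed". The effect is a fall in Type III missed injuries from 14% to 9%.
- Follow-up: the earlier study "achieved a telephone follow-up rate of 40% at 6 months", and the same rate is carried forward to 12 months. From this, "a total of 3,190 patients will be required (1,595 for each cohort) to answer the primary hypothesis".
- Total: a similar sample is added for the before-and-after comparison in Group 2. "This results in a sample of 6,380 patients, with complete 1-year follow-up in at least 2,552".
- Table 3, captioned "Approximate maximum intra-class correlation (ICC) for various cluster sizes and number of intervention hospitals to answer primary hypothesis", counts hospitals per arm. At ICC 0.01 it lists 8, 9 and 10 per arm at cluster sizes 400, 300 and 200.
- The paragraph after Table 3 presents the calculation as agreeing with a published ICC of 0.01 for blunt trauma. It continues: "Assuming an average cluster size of 250 patients, this would mean a total of 3,440 patients would require recruitment (approximately 14 clusters". That total is given as the need of the primary hypothesis. The next paragraph declares the power for that hypothesis adequate.

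**The concern.** The sentence applies an ICC that the authors adopt to a stated cluster size and gives a total for the primary comparison. Its result, about 14 hospitals, makes the planned 16 look comfortable. Yet Table 3, immediately above it, needs 18 hospitals at size 300 and 20 at size 200 for the same ICC. A cluster size of 250 lies between those two, so 14 cannot be right if the table is.

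The statement of adequate power follows directly. The Discussion says that the survey should be abandoned where it is already partly in use if it is not shown to be effective, so a false-negative result would have consequences. Recruitment has not begun, so the figures can still be corrected.

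**Working it through.** **Inputs.** Rates 14% and 9%; alpha 0.05; power 0.80; 638 per group; 40% follow-up; ICC 0.01; cluster size 250; 16 hospitals, 1:1; 3,190 for the primary comparison. All are stated in the article. Sidedness is not stated.

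**Step 1: reproduce 638.** Two-sided, no continuity correction:
n = [1.96·√(2·0.115·0.885) + 0.8416·√(0.14·0.86 + 0.09·0.91)]² / 0.05² = (0.8843 + 0.3785)² / 0.0025 = 637.9, so 638. A one-sided test would give 503, so the plan's figure is two-sided.

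**Step 2: reproduce 3,190.** 2·638/0.40 = 3,190. There is no design effect in it.

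**Step 3: reproduce Table 3.** With DE = 1 + (m − 1)·ICC, hospitals per arm = 638·DE/m, rounded up:

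| m | ICC 0.01 | ICC 0.02 | ICC 0.03 |
|---|---|---|---|
| 400 | 7.96 → 8 | 14.32 → 15 | 20.69 → 21 |
| 300 | 8.49 → 9 | 14.84 → 15 | 21.20 → 22 |
| 200 | 9.54 → 10 | 15.89 → 16 | 22.23 → 23 |

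All nine rows match. They do so only when m is the number of analysed patients, because 638 counts completers.

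**Step 4: apply the same formula at m = 250, ICC 0.01.**

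- *250 analysed.* DE = 1 + 249·0.01 = 3.49. Total = 2·638·3.49 = 4,453. Hospitals per arm = 638·3.49/250 = 8.91, so 9 per arm and 18 in all.
- *250 recruited, 40% followed up.* m = 100 completers, DE = 1 + 99·0.01 = 1.99. Completers = 2·638·1.99 = 2,539; recruited = 2,539/0.40 = 6,348. Hospitals per arm = 638·1.99/100 = 12.7, so 13 per arm and 26 in all (26·250 = 6,500 if all are filled).

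The article states 3,440 and about 14. Since 3,440/250 = 13.8, the 14 is a total over both arms. The figure implies a design effect of 3,440/1,276 = 2.70, not 3.49. The ratios are 4,453/3,440 = 1.3 and 6,348/3,440 = 1.8.

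**Step 5: power with 14 hospitals.** Effective n per arm = k·m/DE, then power = Φ{[0.05·√n − 0.8843]/0.4498}.

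- 7 per arm, 250 analysed: 1,750/3.49 = 501; power 70%.
- 7 per arm, 100 completers: 700/1.99 = 352; power 55%.

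**Step 6: the planned first-year comparison.** 3,190/16 = 199.4 recruited per hospital; ×0.40 = 79.75 completers. DE = 1 + 78.75·0.01 = 1.79. Effective n = 8·79.75/1.79 = 357 per arm; power about 55%. For 80% power: 638·1.79/79.75 = 14.3, so 15 hospitals per arm.

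**The case against.** **Table 3 supports 16 hospitals without this sentence.** Its first row is 8 per arm at size 400 and ICC 0.01. That row reproduces with 80.2% power, and 6,380/16 is 399. So a reader who infers that the faulty sentence is the design's only check on clustering goes too far: Table 3 is such a check, and its arithmetic is sound. This part of the objection stands. It does not rescue the sentence, and the row does not describe the primary comparison. It needs 400 analysed per hospital, whereas 399 is the number recruited over both years, half of it set aside for the Group 2 before-and-after comparison.

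**The figure may come from a one-sided test.** With 503 per arm and everyone followed up, 2·503·3.49 = 3,511 in about 14 clusters, which is close to the printed number. That may be its origin, but it conflicts with the two-sided 638 and with Table 3, and it ignores the 40% follow-up.

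**3,440 exceeding 3,190 is no contradiction in itself.** This is correct. A reader might infer that the trial falls short of its own requirement by 250 patients, but 3,190 is unadjusted for clustering, and an adjusted figure should be larger. The fault is that the text still calls 3,190 required and never carries the adjustment into the total.

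**A larger understatement.** A reader might take 250 as analysed and then divide 4,453 by 0.40, giving 11,133 recruited, or 3.2 times the printed figure. That implies 625 recruited per hospital, while the sentence speaks of patients to be recruited in clusters of 250. The text does not support that reading.

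**Conclusion.** The point holds. The stated 3,440 patients in about 14 clusters is an error on the protocol's own inputs, and Table 3 contradicts it. The requirement is understated 1.3-fold if 250 means analysed patients (4,453 in 18 hospitals) and 1.8-fold if it means recruited patients (about 6,350 in 26 hospitals). The article does not settle which is meant: the wording suggests recruited, while Table 3 reproduces only with analysed. The arithmetic error is confined to this one sentence.

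The weak power of the planned first-year comparison, about 55% at ICC 0.01, is a related but separate consequence of leaving the design effect out of 3,190. Correcting 3,440 alone would not cure it.

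These results assume equal cluster sizes, a normal approximation, a two-sided 0.05 test, 40% follow-up at 12 months, and an ICC of 0.01 for Type III injury. The article reports that ICC as an average and says it varied by outcome.

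**What to change.** 1. State whether cluster size, in the sentence and in Table 3, means recruited patients or completers.
2. Replace 3,440 and 14 with the matching figures: 4,453 analysed in 18 hospitals, or about 6,350 recruited in 26 hospitals (6,500 if all are filled).
3. Add the result at the planned first-year size: 16 hospitals, about 199 recruited and 80 completers each, design effect about 1.79, about 55% power with 8 per arm at ICC 0.01, and about 15 per arm needed for 80%.
4. Label 3,190 as the number before any allowance for clustering, and reconcile it with the corrected figure and with Table 3.
5. Withdraw or restate both the sentence presenting the calculation as consistent with the published ICC and the statement that power for the primary hypothesis is adequate.

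The cost is a change of text only. The stated power becomes less favourable, and the sponsor would then have to decide openly whether to add hospitals, improve follow-up or accept lower power.
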